### Design and participants

The PREDMETH study is a prospective, randomized, non-blinded, multi-center, non-inferiority trial, designed to compare effectiveness and tolerability of methotrexate versus prednisone as first-line therapy for pulmonary sarcoidosis. The study is a joint design of clinicians, scientists and a patient expert panel. In this study, 18 centers in the Netherlands will participate. The study will randomize a total of 138 treatment-naïve adult sarcoidosis patients, about to start first-line therapy for a pulmonary indication.

Patients will be informed about the study by their treating physician. If patients are willing to participate, written informed consent will be obtained, and patients will be screened for eligibility. The in- and exclusion criteria are shown in Table 2. If eligible, patients will be randomized in a 1:1 ratio to receive either prednisone or methotrexate for 24 weeks, after which they will be followed up in regular care up to 2 years. For allocation of each subject to a treatment arm a centralized electronic randomization system will be used. Hospital visits will take place at 4, 16 and 24 weeks, and for long-term follow-up after 1 year and 2 years. Additionally, patients will be asked to perform weekly home spirometry and record symptoms and side-effects via a home monitoring application for 24 weeks.

**Table 2 Tab2:** Inclusion and exclusion criteria

Inclusion criteria	Exclusion criteria
- Diagnosis of sarcoidosis according to the ATS/ERS/WASOG criteria [6], in case of absent histology a diagnosis of sarcoidosis can also be established in a multidisciplinary team meeting in a sarcoidosis expert center based on a highly suggestive clinical and radiological picture [22] - Age ≥ 18 years - A pulmonary indication for treatment and parenchymal involvement on X-ray or chest CT-scan conducted within three months before inclusion (determined by the treating physician and according to current guidelines) - A forced vital capacity (FVC) of ≤90% of predicted, or a diffusion capacity of the lung for carbon monoxide (DLCO) ≤70% of predicted, or an absolute decline of ≥5% FVC decline, or an absolute ≥10% DLCO decline in the past year	- Any condition or circumstance that, in the opinion of the investigator, may make a subject unlikely or unable to complete the study or comply with study procedures - Previous immunosuppressive treatment for sarcoidosis - Use of systemic immunosuppressive therapy within the preceding three months for another disease than sarcoidosis - Pregnant, breastfeeding, or planning to become pregnant or breastfeed during the study treatment or within 90 days after the last dose in the randomized study phase. For males; planning to pro-create during the study or within 90 days after the last dose of the randomized study phase - Primary systemic treatment indication being an extra pulmonary location of sarcoidosis (e.g. cardiac of neurological) - Contra-indication for methotrexate or corticosteroids^a^

^a^Contra-indications for methotrexate or corticosteroids are defined as: severely impaired renal function (creatinine clearance < 30 ml/min), impaired hepatic function (serum bilirubin-value > 5 mg/dl or 85,5 μmol/l), bone marrow insufficiency with severe leukopenia, thrombocytopenia, or anaemia, severe acute or chronic infections, such as tuberculosis, human immunodeficiency virus, parasitic infections or other immunodeficiency syndromes, mouth, stomach or duodenal ulcers

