### Treatment schedule

For prednisone the standard dosage according to literature is 20–40 mg daily [3, 7]. Patients will start with 40 mg prednisone daily for 4 weeks. Subsequently, this dose will be tapered to a maintenance dose of 10 mg/day within 16 weeks. The maintenance dose will be continued until 24 weeks after start of treatment. After 24 weeks, the prednisone is either continued at 10 mg or further reduced at the discretion of the treating physician. According to current clinical recommendations patients will also receive calcium 500 mg /colecalciferol 400 IE per day (6 days per week) and risedronic acid 35 mg once a week. In case of intolerable side-effects of prednisone, the treating physician will start early tapering. If side-effects remain intolerable, prednisone will be discontinued and patients will start on the methotrexate schedule.

For methotrexate, the starting dosage will be 15 mg once a week, with folic acid 5 mg once a week. Subsequently, the dose will be increased to 25 mg/week within 8 weeks if tolerated. After 24 weeks, the dose of methotrexate is either continued or reduced at the discretion of the treating physician. Methotrexate will be discontinued if aspartate aminotransferase (AST) is > 3 times the upper limit of normal. In case of intolerable side-effects of methotrexate the total dose will be divided in twice weekly. If side-effects do not subside, oral methotrexate will be switched to subcutaneous methotrexate in the same dose. If side-effects remain intolerable, dosage of subcutaneous methotrexate will be tapered according to the discretion of the treating physician. If side-effects do not subside, methotrexate will be discontinued and the patient will start on the prednisone schedule. If an absolute FVC decline of ≥10% on in-hospital measurement of FVC is detected, the other treatment arm will be added to the current therapy (i.e. patients on methotrexate will additionally start with the prednisone schedule and patients on prednisone will additionally start with the methotrexate schedule). In this case, patients will be treated with both methotrexate and prednisone and remain in the study. At any time, the treating physician may decide to deviate from this treatment schedule if the clinical situation demands so. Figure 1 shows the treatment schedule of prednisone and methotrexate.

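### The hepatic contra-indication at entry is bilirubin only, so a patient already above the methotrexate AST stopping limit meets no named exclusion

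*Protocol article*

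**What the plan says.** **Entry.** Under Design and participants, Table 2 excludes patients with a contra-indication to either study drug. Footnote a closes that term with a definition: "Contra-indications for methotrexate or corticosteroids are defined as", followed by a list. The only liver item is "impaired hepatic function (serum bilirubin-value > 5 mg/dl", also given as 85.5 μmol/l. Neither the footnote nor the exclusion list contains an AST, ALT or liver-disease criterion. The first exclusion criterion is a general one, left to the investigator's opinion, for subjects "unlikely or unable to complete the study or comply with study procedures".

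**Stopping.** Under Treatment schedule: "Methotrexate will be discontinued if aspartate aminotransferase (AST) is > 3 times the upper limit of normal". The rule makes no reference to the patient's baseline value. The same section adds a general discretion: "At any time, the treating physician may decide to deviate from this treatment schedule".

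**Prednisone patients who later receive methotrexate.** There are two routes. For intolerance that persists after early tapering: "If side-effects remain intolerable, prednisone will be discontinued and patients will start on the methotrexate schedule". For an absolute FVC decline of 10% or more: "patients on prednisone will additionally start with the methotrexate schedule".

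**Order of events.** Before randomisation, "written informed consent will be obtained, and patients will be screened for eligibility". The Hospital visits section includes liver function among the routine blood tests but attaches no entry threshold to it.

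**The concern.** Allocation is random and each arm can switch to the other drug or add it, so every patient entered should be fit to start either drug. The contra-indication criterion exists to secure this. For the liver it does not, because entry is judged on bilirubin and continuation of methotrexate on AST. A patient can pass the first and fail the second on the same blood sample.

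The stopping rule itself is sound; the gap is in the entry list. What is at stake is chiefly patient safety and the sense of the allocation, since a patient could be randomised to a drug that the protocol requires to be stopped. Such a patient would also be counted under medication discontinuation or switching, and under adherence (both secondary endpoints in Table 1), because of a condition present at entry and not because the drug was poorly tolerated. The AST rule applies only to methotrexate, so this would fall mainly on one arm.

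**Working it through.** **1. The plan's own figures.** The two bilirubin units agree: 5 mg/dl × 17.1 = 85.5 μmol/l. The sample size also reproduces. With SD 10.5, margin 5, one-sided α 5%, power 80% and no true difference:

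- n per arm = 2 × (1.645 + 0.842)² × 10.5² / 5² ≈ 54.5, rounded up to 55, or 110 in total
- 110 / (1 − 0.20) = 137.5, rounded up to 138

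The concern does not depend on this calculation, but 138 randomised 1:1 gives the 69 per arm used below.

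**2. The two rules applied to one patient.** Take AST at 4 times the upper limit and bilirubin of 2 mg/dl, with all else acceptable.

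| Rule | Test | Result |
|---|---|---|
| Footnote a, hepatic item | bilirubin > 5 mg/dl | not met |
| Other named exclusions | none uses a transaminase | not met |
| Investigator-opinion exclusion | judgement, no liver value | may or may not be used |
| Methotrexate stopping rule | AST > 3 times the upper limit | met before the first dose |

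The same holds for any patient with AST above 3 times the limit and bilirubin at or below 5 mg/dl who meets no other exclusion.

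**3. How many patients.** The documents give no frequency of AST above 3 times the limit at entry, so a prevalence p of 0.2% to 1% is assumed. For the 69 methotrexate patients, the expected number is 69p and the chance of at least one is 1 − (1 − p)^69.

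| p (assumed) | Expected number | Chance of at least one |
|---|---|---|
| 0.2% | 0.14 | 0.129 |
| 0.5% | 0.35 | 0.292 |
| 1% | 0.69 | 0.500 |

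**4. Prednisone patients who reach methotrexate.** Assume a share s of 5% to 20% (3.45 to 13.8 of 69). The additional expected number is 69sp:

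- s = 0.05, p = 0.002: 0.007
- s = 0.20, p = 0.01: 0.138

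For both groups together the chance of at least one is 1 − (1 − p)^(69(1 + s)):

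- s = 0.05, p = 0.002: 0.135
- s = 0.20, p = 0.01: 0.565

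**5. Direction of error.** These figures ignore the investigator-opinion exclusion and the likelihood that physicians would not refer such patients. For any given p they are therefore upper values.

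**The case against.** The strongest reply is that the patient is already covered. Someone whose screening AST meets the stopping rule cannot follow the methotrexate schedule, so the investigator-opinion exclusion can be applied. If the patient is entered anyway, routine liver tests, a mandatory stopping rule and the physician's freedom to deviate all protect them. Entry and stopping rules have different purposes and need not share a marker. An added entry line would also be defeated by the same oversight that would lead to harm, because someone still has to read the AST.

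Much of this stands as an argument about size. It does not close the gap: the discretionary exclusion names no liver value and would be applied separately in 18 centres, and the other safeguards act on treatment after randomisation.

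A second reply is that this is a condensed article. Laboratory limits may sit in the full protocol, and the study schedule (Table 3) and treatment flow chart (Fig. 1) cannot be seen here. That would answer a complaint about missing detail. This point concerns two printed rules with numeric limits, one of them worded as a definition. If the full protocol does hold an AST entry limit, footnote a misreports it and the same correction applies.

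A third reply is that the prevalence and the switching share are both assumed. This is correct: the calculation shows only what those assumptions imply. The objection to the prednisone step also stands. What matters there is AST when methotrexate is started, which an entry limit does not control, so that step should carry little weight.

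**Conclusion.** The point holds as a minor safety mismatch. As written, the named entry limits allow randomisation to methotrexate of a patient for whom the protocol already requires it to be stopped. This follows from the text and needs no assumption.

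The size does rest on assumptions. At a prevalence of 0.2% to 1%, fewer than one methotrexate patient is expected, with a 13% to 50% chance of at least one. Including prednisone patients who later receive methotrexate makes this 14% to 56%, with the reservation given above. The realistic result is methotrexate withheld or stopped at once; harmful exposure would require the abnormal AST to be missed. Sample size, power and the FVC conclusion do not change. The correction is optional, and worth making because it is nearly free.

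**What to change.** Extend the hepatic item of footnote a in Table 2 to bilirubin > 5 mg/dl **or AST > 3 times the upper limit of normal**, checked on the routine bloods at eligibility screening, before randomisation. The threshold is the sponsor's own stopping limit, so no new cut-off has to be justified, and no patient eligible on that screening sample could already meet the stopping rule on it.

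The cost is one line. An eligibility screen before randomisation already exists, liver function is already among the routine bloods, and the bilirubin item already presupposes a liver result before entry. The downside is that a very few patients become ineligible. The sample size needs no change.

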### Hospital visits

Baseline characteristics of patients, such as gender, age, self-reported ethnicity, smoking status, comorbidity, co-medication, date of sarcoidosis diagnosis, details of organ involvement, and if available details of x-ray and chest CT scan will be recorded. At every visit, a physical examination will be performed to record weight, height, waist circumference and blood pressure of the patients. In-hospital pulmonary function measurements will include FVC, Forced Expiratory Volume in 1 second (FEV1) and diffusion capacity of the lung for carbon monoxide (DLCOc). Furthermore, routine blood samples will be collected to assess blood count, kidney- and liver function. An additional sample of 80 ml blood will be taken for analysis of Angiotensin coverting enzyme (ACE), Serum soluble interleukin-2 receptor (sIL-2R), monocyte subsets, T-cells, dendritic cells, and proteomics biomarker discovery. Patients will also be asked to complete patient-reported outcome measures (PROMs) via a home monitoring app at every visit. The PROMs consist of the Fatigue Assessment Scale (FAS), the King’s Sarcoidosis Questionnaire (KSQ), Global Rating of Change Scale (GRoC), Chronic Respiratory Questionnaire (CRQ), Patient Experience and Satisfaction with Medication Questionnaire (PESaM) and Euroqol-5D-5L questionnaire (EQ-5D-5L). At follow-up visits all adverse events will be evaluated and recorded. Side-effects will be managed according to the discretion of the treating physician. Physicians can deviate from the treatment flowchart at any time, if the clinical situation demands so. The study design is shown in Table 3.

**Table 3 Tab3:**
[figure not shown]
Study schedule of the PREDMETH study

### Treatment schedule

For prednisone the standard dosage according to literature is 20–40 mg daily [3, 7]. Patients will start with 40 mg prednisone daily for 4 weeks. Subsequently, this dose will be tapered to a maintenance dose of 10 mg/day within 16 weeks. The maintenance dose will be continued until 24 weeks after start of treatment. After 24 weeks, the prednisone is either continued at 10 mg or further reduced at the discretion of the treating physician. According to current clinical recommendations patients will also receive calcium 500 mg /colecalciferol 400 IE per day (6 days per week) and risedronic acid 35 mg once a week. In case of intolerable side-effects of prednisone, the treating physician will start early tapering. If side-effects remain intolerable, prednisone will be discontinued and patients will start on the methotrexate schedule.

For methotrexate, the starting dosage will be 15 mg once a week, with folic acid 5 mg once a week. Subsequently, the dose will be increased to 25 mg/week within 8 weeks if tolerated. After 24 weeks, the dose of methotrexate is either continued or reduced at the discretion of the treating physician. Methotrexate will be discontinued if aspartate aminotransferase (AST) is > 3 times the upper limit of normal. In case of intolerable side-effects of methotrexate the total dose will be divided in twice weekly. If side-effects do not subside, oral methotrexate will be switched to subcutaneous methotrexate in the same dose. If side-effects remain intolerable, dosage of subcutaneous methotrexate will be tapered according to the discretion of the treating physician. If side-effects do not subside, methotrexate will be discontinued and the patient will start on the prednisone schedule. If an absolute FVC decline of ≥10% on in-hospital measurement of FVC is detected, the other treatment arm will be added to the current therapy (i.e. patients on methotrexate will additionally start with the prednisone schedule and patients on prednisone will additionally start with the methotrexate schedule). In this case, patients will be treated with both methotrexate and prednisone and remain in the study. At any time, the treating physician may decide to deviate from this treatment schedule if the clinical situation demands so. Figure 1 shows the treatment schedule of prednisone and methotrexate.

**Fig. 1 Fig1:**
[figure not shown]
Flow chart of the treatment schedule for methotrexate and prednisone during the randomisation phase

### Home monitoring

For home monitoring of pulmonary function, symptoms and side-effects, a home monitoring application will be used, which has previously been developed together with sarcoidosis patients [21]. The application will be installed on a smartphone or tablet. In this CE-marked, secured application (Curavista, the Netherlands), patients will keep track of their own data, such as pulmonary function, side-effects and symptoms. A graphic overview of results is available, so patients can gain more insight in their disease course, an example is shown in Fig. 2. A handheld spirometer (Spirobank Smart, MIR, Italy) will be handed out to all patients. Patients will be instructed to undertake spirometry (three consecutive measurements) once a week at the same day, at approximately the same time to enhance compliance and reduce variability [23]. The best result of the day will be transmitted real-time to the patients’ personal platform and will be directly accessible for both patients and the study team. This will enable close monitoring and early detection of possible deterioration. On the same day as spirometry, patients will report their symptoms and, if any, side-effects on their personal platform. Patients record cough, dyspnea, fatigue, and general complaints on a visual analog scale (VAS) and will also report dyspnea on the Medical Research Council scale (MRC). In case of side-effects, patients can record which side-effects they have and how bothersome they are. When FVC declines ≥10%, or side-effects are burdensome, an email alert will be sent directly to the treating physician, who will contact the patient within 24 h to discuss symptoms and decide whether an extra outpatient clinic visit with pulmonary function measurement is needed. Furthermore, patients will be asked to complete PROMs at every time point before the doctor’s visit.

**Fig. 2 Fig2:**
[figure not shown]
Example of Home spirometry outcome, this graphical overview is available on patient’s personal platform and is accessible for both patients and the study team

### Serum and cellular biomarkers

Blood samples will be analyzed in order to study both serum and cellular biomarkers. With regards to serum biomarkers, the value of existing biomarkers such as ACE and sIL-2R in predicting disease progression or response to therapy will be studied prospectively. Furthermore, a proteomics approach will be used to search for possible new biomarkers in sarcoidosis. Regarding cellular biomarkers, the amount of Th17-lineage cells, DCs and monocytes will be analyzed in order to predict response for individual patients to prednisone and/or methotrexate.

### Sample size calculation

The power calculation is based on data from a previous observational study with prednisone in newly treated patients with pulmonary sarcoidosis. In this study, the mean increase in FVC with prednisone was 15%, with a standard deviation of 10.5% [8]. In a case series of 50 patients with sarcoidosis treated with methotrexate, treatment effect was in line with the findings for prednisone; 66% of patients had more than 15% improvement in vital capacity after 6 months [24]. We chose a non-inferiority margin of 5%, because FVC measurements show biological variation and thus variation < 5% is not considered clinically relevant. Based on these numbers, using a one-sided test with a power of 80% (β) and a type 1 error of 5% (α), the estimated sample size of this study is 110 patients. To allow for 20% drop-out, we aim to randomize 138 patients.

### Statistical analyses

The primary analysis will be based on the Intention-to-Treat (ITT) population, defined as all randomized patients who received at least one dose of prednisone or methotrexate. Patients who discontinue treatment prematurely will be analyzed based on the available data. As a sensitivity analysis, a Per Protocol analysis will be performed in all enrolled patients who complete the 24 week treatment regimen without major protocol violations. Change in FVC (% predicted) between baseline and 24 weeks follow-up will be compared between the two groups by using multilevel analysis with the repeated values of FVC as dependent variable and groups, time (defined as categorical variable) and baseline FVC as covariate. To account for the repeated FVC measurements, patient will be included as a random effect. Additionally the interaction terms between the time points and group will be added to assess at which point in time the groups have different average FVC values.

(Generalized) multilevel analyses will also be used to evaluate within and between-group differences in pulmonary function, symptoms, QoL scores, and side-effects over the study period. Between-group differences in mean time to onset of side-effects and time to symptom improvement will be analyzed using Kaplan Meier and log rank test. The Chi square test will be used to evaluate between-group differences in the proportions of patients who discontinue medication, proportion of patients who have FVC improvement and FVC decline, and the proportion of patients who adhere to the treatment schedule. The time to pulmonary improvement, using home spirometry, will be assessed using a linear mixed model, with FVC as dependent variable and time and treatment group as independent variables. Time will be entered as a random effect and will be modelled flexible. Moreover, this model will incorporate the change in curvature of the FVCs temporal trajectory, and thus enable estimation of the time point at which the maximum improvement in lung function is reached. Correlation between lung function, side-effects, QoL scores and symptoms will be analyzed with Pearson Correlation Coefficient. The FVC trajectory over time will be related to the trajectory of QoL scores over time with a linear mixed model. Logistic regression will be used to analyze which clinical or laboratory parameters are associated with disease progression (defined as ≥10% FVC decline) and disease chronicity.

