## Methods/design

### Objectives and endpoints

The main objective of this study is to investigate the effectiveness and tolerability of methotrexate as first-line therapy in patients with pulmonary sarcoidosis compared with prednisone. The primary endpoint of this study is the change in hospital-measured Forced Vital Capacity (FVC) between baseline and 24 weeks. Secondary objectives are to gain more insights in response to therapy in individual patients by home spirometry and patient reported outcomes. Furthermore, we aim to also examine blood biomarkers of disease progression and chronicity, to assess whether response to therapy can be predicted in individual patients, and to gain more insights into the underlying disease mechanism and potential new targets for therapy. Table 1 shows the endpoints of the PREDMETH study.

**Table 1 Tab1:** Endpoints of the PREDMETH study listed as primary endpoint, secondary endpoints and explorative endpoints

Primary endpoint	
- Between-group difference in change in hospital-measured Forced Vital Capacity (FVC) % predicted between baseline and 24 weeks	
Secondary endpoints	

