Next to side-effects and symptoms, the home monitoring program also allows for close monitoring of lung function. A previous observational study in patients with pulmonary sarcoidosis, newly treated with prednisone, showed that home spirometry can reliably detect changes in pulmonary function in sarcoidosis patients and assess the time to pulmonary improvement [8]. The major increase in FVC already occurred within the first month of treatment; however, until now no consensus exists on the optimal tapering schedule [7]. The PREDMETH trial will also provide data on time to pulmonary improvement in patients treated with methotrexate, which are currently lacking. The online home monitoring program that will be used in the current study, has been previously evaluated together with sarcoidosis patients in a pilot study. This study showed that patient satisfaction and compliance were high, and the reproducibility of FVC was good [21]. Thus, home monitoring will allow us to better evaluate (early) response to therapy, could enable personalized tapering of medication in the future and will provide more insights in the balance of effects and side-effects in newly-treated sarcoidosis patients.

Next to the important clinical aims of the study, the role of serum and cellular biomarkers in disease pathogenesis as well as predicting disease outcome will be further explored [26]. By combining these insights with the clinical outcomes of the study this trial will hopefully provide unique insights in the development and disease course of pulmonary sarcoidosis.

In conclusion, by conducting a randomized clinical trial to compare prednisone and methotrexate as first line treatment of pulmonary sarcoidosis we expect to advance evidence based treatment practice for sarcoidosis. Furthermore, seamlessly integrating translational research on patient samples from this trial will provide more insights not only with regard to tailored treatment, but also in the pathophysiological mechanisms of sarcoidosis. All together, we believe that the proposed study has the potential to enhance evidence-based and personalized therapy that improves outcomes and quality of life for patients with sarcoidosis.

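### The stated primary model, with a patient random effect only, keeps the one-sided 5% non-inferiority error only if FVC variance is about equal at weeks 4, 16 and 24

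*Protocol article*

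**What the plan says.** The primary endpoint (Protocol article, Objectives and endpoints, Table 1) is the "Between-group difference in change in hospital-measured Forced Vital Capacity (FVC) % predicted between baseline and 24 weeks". On visit timing, Design and participants says: "Hospital visits will take place at 4, 16 and 24 weeks, and for long-term follow-up after 1 year and 2 years".

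The section Statistical analyses describes the primary model as a "multilevel analysis with the repeated values of FVC as dependent variable and groups, time (defined as categorical variable) and baseline FVC as covariate". Dependence within patients is dealt with in one sentence: "To account for the repeated FVC measurements, patient will be included as a random effect". On the interaction it says: "Additionally the interaction terms between the time points and group will be added". The model therefore yields a separate group difference at week 24.

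No random time effect and no residual covariance structure are named for this model. For the home-spirometry model in the same section, a random time effect is named: "Time will be entered as a random effect and will be modelled flexible".

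The only SD for FVC is in Sample size calculation: "the mean increase in FVC with prednisone was 15%, with a standard deviation of 10.5" (percent). It is not tied to a visit. The same section sets a 5% margin, a one-sided 5% test, 80% power, 110 patients, and 138 after allowing for 20% drop-out.

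**The concern.** A patient random intercept with independent, constant-variance residuals is compound symmetry: one variance for all visits and one correlation for every pair of visits. Non-inferiority, however, is judged at one visit. If FVC, after adjustment for baseline, scatters more at week 24 than on average over weeks 4, 16 and 24, the model gives the week-24 difference too small a standard error and too narrow a confidence interval. In a non-inferiority trial, an interval that is too narrow makes it too easy to exclude the margin. If the scatter is smaller at week 24, the opposite happens: the interval is too wide and power is lost.

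Rising scatter is plausible but not documented. The section Treatment schedule has each arm start on a common regimen. Tapering, tolerance-dependent escalation, switching, add-on treatment and physician deviation come later.

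**Working it through.** **Inputs from the Protocol article.** Margin 5, SD 10.5, one-sided alpha 5% (z = 1.645), power 80% (z = 0.842), 1:1 allocation, 20% drop-out, outcome visits at weeks 4, 16 and 24 with baseline as a covariate.

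**Assumptions.** The SD of 10.5 is placed at week 24. The SDs at weeks 4 and 16 are assumed and varied.

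**1. The plan's own figure.** n per arm = 2 × (1.645 + 0.842)² × 10.5² / 5² = 54.5, so 55 per arm and 110 in total. 110 / 0.8 = 137.5, so 138. Both stated figures are reproduced.

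**2. What the random-intercept model uses at week 24.** Let V be the true 3 × 3 covariance of the visits after adjustment for baseline, and S the sum of all its elements. With complete, balanced data and a group-by-time term:

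- the between-patient mean square estimates S/3
- the within-patient mean square estimates (trace V − S/3)/2
- the model variance at any visit is (2/3) × within + (1/3) × between = (trace V − S/3)/3 + S/9 = trace V / 3

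This is the plain average of the three visit variances. The off-diagonal terms cancel, so correlation, and with it visit spacing, drops out of the standard error of the week-24 difference. Only unequal variance matters.

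**3. Effect on the error rate.** Ratio = model SE / true SE = √(mean visit variance) / 10.5. Actual one-sided error = 1 − Φ(1.645 × ratio).

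| Assumed SD at weeks 4 / 16 / 24 | Mean variance | Square root | Ratio | Actual error |
|---|---|---|---|---|
| 12 / 11 / 10.5 | 375.25/3 = 125.08 | 11.18 | 1.07 | 4.0% |
| 10.5 / 10.5 / 10.5 | 330.75/3 = 110.25 | 10.50 | 1.00 | 5.0% |
| 9 / 10 / 10.5 | 291.25/3 = 97.08 | 9.85 | 0.94 | 6.1% |
| 8 / 9.5 / 10.5 | 264.5/3 = 88.17 | 9.39 | 0.89 | 7.1% |
| 7 / 9 / 10.5 | 240.25/3 = 80.08 | 8.95 | 0.85 | 8.0% |

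**4. Check by simulation.** For SDs 7/9/10.5, 20,000 simulated trials gave an error of 7.9% with the random-intercept model and 4.9% with visit-specific variances.

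**5. Does correlation matter on its own?** REML random-intercept fits were simulated with 69 patients per arm, equal SDs of 10.5, serial correlation of 0.9 or 0.7 per 8 weeks, and 0% or 20% random drop-out (1,500 runs each). The SE ratio was 0.98 to 1.02 and the error 4.9% to 5.7%, with Monte Carlo uncertainty of about ±1.1 points. This agrees with step 2: no material effect.

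**The case against.** **The article is a condensed account.** It states no residual structure, and a patient random effect can be combined with visit-specific or autocorrelated residuals. A reader might infer that the plan forces equal variance and equal correlation. The text does not go that far: compound symmetry follows only with default residuals, and the full protocol or SAP may say otherwise. This stands, and it makes the point conditional. It does not remove it, because the patient random effect is the only device the article names for the primary model. The contrast with the home-spirometry model is weak evidence, since that model describes weekly trajectories and not three categorical visits.

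**Unequal spacing.** The gaps between visits make it tempting to blame the equal-correlation assumption. Steps 2 and 5 show that this does not matter for the week-24 standard error.

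**Missing data.** A reader might also infer that a wrong correlation, with 20% drop-out, materially biases the week-24 comparison. This is not supported. With equal SDs and drop-out that depends on the week-16 value, the week-24 mean of one arm moved by only about 0.05 to 0.3 points against a margin of 5, and the shift cancels between arms if they lose patients in the same way. Larger shifts (0.6 to 0.7 points in one arm with SDs 7/9/10.5) again come from the assumed unequal variances.

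**Direction.** It is tempting to take a rising SD for granted. The Discussion says of prednisone that "The major increase in FVC already occurred within the first month of treatment", so differences in response could already be present at week 4. Adding the other drug after an FVC decline could also limit late scatter. Neither shows that the SD is flat or falling, but nothing in the article shows that it rises. This objection stands in full.

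**Conclusion.** The point holds as a conditional weakness and not as a demonstrated error. Read as written, with default residuals, the primary model controls the one-sided error at 5% only if FVC variance is about equal at weeks 4, 16 and 24. Under the assumed SDs the actual error runs from about 4% to about 8%, and that range includes no error at all; the 8% is the steepest of the scenarios tried. The result rests on three assumptions: default residuals, assumed SDs at weeks 4 and 16, and the single published SD of 10.5 being the one at week 24. A random-intercept model is a recognised analysis and contradicts nothing else in the article. The case for changing it is that a model without the equal-variance assumption costs almost nothing and is valid whichever way the variance runs.

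**What to change.** In the primary model, replace the patient random intercept by an unstructured covariance over weeks 4, 16 and 24, fitted by REML with Kenward-Roger degrees of freedom. Keep the fixed terms as they are, and take the non-inferiority interval from the week-24 contrast. Do not keep a patient random intercept alongside the unstructured matrix, because it would be redundant.

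State a fallback order in advance for non-convergence: heterogeneous Toeplitz, which still allows a separate variance at each visit, and then a random intercept with robust standard errors.

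The cost is one or two sentences in the analysis section. The covariance has six parameters instead of two, which 110 to 138 patients support easily. No extra patients, visits or data are needed, and the sample size is unaffected. If the full protocol or SAP already fixes such a structure, confirming it is enough.
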